### Data monitoring

3.16

An independent data monitoring committee (DMC) consisting of neurologists, assessors, and data analysts from West China Hospital will check the data once a year to guarantee the efficacy and safety and of this trial.

All adverse events will be recorded in detail, properly handled and tracked until they were properly resolved or stable, and be timely reported to ethics committee and competent department. We will conduct cumulative review on all adverse events on a regular basis, and convene a meeting of researchers to assess the risk of the study if necessary.

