### Study design

3.2

We will conduct a monocentric, assessor-blinded, and randomized controlled trial titled “Comparison of Ventriculoperitoneal Shunt to Lumboperitoneal Shunt for the treatment of Idiopathic Normal Pressure Hydrocephalus: Phase I (COVLINPH-1)” trial and recruit patients at West China Hospital of Sichuan University since June 2021. And this trial is expected to end in December 2030. Eligible participants will be randomly assigned into LPS group and VPS group at ratio of 1:1 followed by evaluation before surgery, 1 month, 12 months, and 5 years after surgery. The primary outcome is the rate of shunt failure within 5 years. The secondary outcomes include modified Rankin Scale (mRS), INPH grading scale (INPHGS), mini-mental state examination (MMSE), and Evans index. We will calculate the rate of favorable outcome, which is defined as shunt success and an improvement of more than 1 point in the mRS at evaluation point. We will also analyze the complications throughout the study within 5 years after shunt insertion.

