### Randomizing and blinding

3.7

This trial is randomized and open-label. We will complete the randomization through a random number table, but the data collectors, accessors, and analysts are blinded to allocation.

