### Outcomes

3.11

Evaluation schedule is shown in Fig. 1. Each participant is evaluated before surgery, 1 month, 12 months, and 5 years after surgery by 2 independent assessors.

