### Statistics analysis

3.15

We will use SPSS 19.0 software to analyze the data. The statistical description of categorical variables adopts number (percentage). For continuous data, firstly, the Kolmogorov Smirnov test will be used to analyze the normality. The statistical description in accordance with the normal distribution is mean ± standard deviation (SD), and the median (range) description is used for those do not follow the normal distribution. Wilcoxon rank sum test or *t* test is used to compare the difference of continuous data according to the normality. Chi-Squared test is used to compare the difference of categorical variables. Kaplan–Meier survival analysis is used to draw the shunt-success curve. In this study, *P* value under .05 is considered to be statistically significant.

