In terms of the definition of “normal pressure,” it is different between Western guideline and Japanese guideline. The CSF opening pressure measured by lumbar puncture in the lateral recumbent position is in the range of 70 to 245 mm H_2_O according to the Western guideline, comparing to a CSF opening pressure under 200 mm H_2_O based on Japanese guideline. Taken together, a range of 70 to 200 mm H_2_O is considered in this study since pressures that are dramatically higher or lower than this range are not accordant with a probable NPH diagnosis, as well as not suitable for the upcoming LPS surgery.

This trial will the first randomized controlled trial that compares the long-term outcomes of VPS with that of LPS in the treatment of INPH. The results of this trial will provide certain evidence for the treatment option for patients with INPH. This trial will also generate the discussion regarding this subject. In addition, based on this trial, we could analyze the related factors of shunt failure in patients with INPH to exclude the patients with high risk of shunt failure.

This trial has some limitations. First, it is single-center study. Second, the shunting outcomes are possibly associated with personal experiences and qualifications. In this regard, we will propose a uniform standard and surgeons will be trained before recruitment.

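### The data monitoring committee is called independent but is formed from assessors and data analysts of the trial's only site, roles that the protocol elsewhere keeps blinded

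*Protocol article*

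**What the plan says.** Section 3.16 (Data monitoring) fixes who sits on the committee: "An independent data monitoring committee (DMC) consisting of neurologists, assessors, and data analysts from West China Hospital will check the data once a year". It gives the purpose in the same sentence: the committee "will check the data once a year to guarantee the efficacy and safety" of the trial.

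Section 3.2 (Study design) says that the trial will "recruit patients at West China Hospital of Sichuan University since June 2021", and the limitations in Section 4 (Discussion) confirm that "it is single-center study". All committee members therefore come from the one hospital that runs the trial.

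Section 3.7 (Randomizing and blinding) says "This trial is randomized and open-label", and adds that "the data collectors, accessors, and analysts are blinded to allocation" (accessors is evidently a misprint for assessors). Section 3.11 (Outcomes) has each participant evaluated before surgery and "1 month, 12 months, and 5 years after surgery by 2 independent assessors".

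Section 3.15 (Statistics analysis) gives one general threshold: a P "value under .05 is considered to be statistically significant".

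**The concern.** A monitoring committee is normally kept apart from the trial team so that it can look at accumulating data by group without affecting how the trial is run, scored or analysed. Section 3.16 uses the word independent, but then names the functions that Section 3.7 shields from knowledge of allocation. The two sections sit badly together, and the conflict lies in what the article states. It is not a detail that the article has left to another document.

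Patients and surgeons know which shunt was placed, so the remaining safeguard against biased measurement is that assessors and analysts do not know. mRS, INPHGS and MMSE depend on a rater, and mRS also enters the definition of favorable outcome in Section 3.13. An assessor who has seen how the groups compare may score later visits differently. An analyst who has seen the same may make different choices in the final analysis. Blinding lost in this way cannot be restored afterwards.

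**Working it through.** The document gives no figure for the committee or for its reviews, so there is none to reproduce. The check sets the sections side by side and then looks at the calendar.

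**Step 1: roles.**

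| Role | Section 3.16 | Section 3.7 |
|---|---|---|
| Assessors | On the committee | Blinded |
| Data analysts | On the committee | Blinded (analysts) |
| Neurologists | On the committee | Not mentioned |
| Data collectors | Not named | Blinded |

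Two of the three committee roles are also two of the three blinded roles. Assessors is the article's own word for those who evaluate outcomes (Section 3.11), and Section 3.16 does not mark its assessors as different people.

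**Step 2: site.** The committee is drawn wholly from one hospital (Section 3.16), and that hospital is the only site (Sections 3.2 and 4). Nothing in the article places any member outside the trial team.

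**Step 3: timing.** Inputs: start June 2021 and expected end December 2030 (Section 3.2); yearly checks (Section 3.16); assessments at 1 month, 12 months and 5 years (Section 3.11). Assumption: the first check comes one year after recruitment opens.

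- First possible 5-year assessment: June 2021 + 5 years = June 2026.
- Checks before that date: June 2022, 2023, 2024 and 2025, so at least four.
- For any one participant, the time from the 12-month to the 5-year assessment is 5 − 1 = 4 years, which holds about four yearly checks.

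The 5-year scores, which carry the long-term comparison, would thus all be made after repeated committee reviews.

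**Step 4: what the committee might see.** Section 3.16 does not say whether data are shown by group.

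- If they are, and members are also trial assessors or analysts, those people learn results by group while follow-up continues.
- If only pooled data are shown, blinding is safe, but the committee cannot compare harm or benefit between the two shunts, which its stated purpose seems to need.
- If groups are shown under codes, individual allocations are not revealed directly, but a trial analyst on the committee would still follow the difference between groups as it develops.

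The present membership is harmless only under conditions that the section does not state.

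**Step 5: false-positive rate.** Section 3.16 describes no hypothesis test. With no formal efficacy test at the yearly checks, the type I error of the final test stays at the planned two-sided 5% (Section 3.6).

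**The case against.** The strongest reply is that the conflict is one of role names. Section 3.16 does not say that its assessors are the two of Section 3.11, that its data analysts are those who will run the final analysis, or that anyone sees results by named group. Employment at the same hospital weakens independence but does not prove involvement in the trial. All of this stands. A reader might infer that the committee will unblind the trial, and the document does not support so firm a statement. It supports only that nothing stated prevents it.

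It can also be said that safety does not rest on the committee alone. The second paragraph of Section 3.16 has all adverse events recorded, followed and reported to the ethics committee, with regular cumulative review. That stands too, and it answers a charge that patients go unprotected. It does not answer the question of who sits on the committee.

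A further reply is that the argument bears on secondary outcomes. The primary outcome in Section 3.12 is shunt failure, largely a matter of device events and revision, and no bias in it has been shown. This limits the reach of the point but leaves the rater-scored scales and the final analysis exposed.

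A stronger reading is also tempting: that yearly checks naming efficacy, together with the .05 threshold of Section 3.15, amount to repeated testing without error control. If every check were a formal test at two-sided .05 with equal information steps, the overall type I error would be about 14% for five looks and 19% for nine (14.2% and 18.6% by simulation under no difference). The document does not support this reading. It describes no interim test, stopping rule or threshold for the yearly check, the .05 is its general significance level, and interim boundaries are commonly left to documents not shown here.

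**Conclusion.** The point holds as a stated conflict between Sections 3.16 and 3.7. A committee called independent is made up of staff of the only site, and two of its three named roles are ones that the protocol keeps blinded in an open-label trial. Its consequence is conditional on two things that the text leaves open: that the same people serve in both capacities, and that they see data by group. If both are true, assessors and analysts could know results by group through at least four yearly checks before any 5-year assessment is made, given a first check one year after recruitment opens. The document offers no basis for putting a number on the resulting bias. Neither certain unblinding nor an inflated false-positive rate is part of the conclusion. The point still merits correction, because the change is small and a loss of blinding cannot be repaired.

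**What to change.** Amend Section 3.16 to state that:

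1. no trial assessor, data collector or trial analyst sits on the committee;
2. their places are taken by clinicians and a statistician who are not involved in the trial;
3. data by group go only to those members;
4. the yearly check includes no formal efficacy test, so that the type I error stays at 5%.

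The cost is a change of membership, by replacement and not by addition, and a short amendment. It requires no extra patients, visits or follow-up.

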## Discussion

4

This study is designed to highlight the controversy concerning INPH treatment options. To address the highlight, each participant will be followed up to 5 years after shunts to compare the long-term outcomes of VPS cohorts with that of LPS cohorts. The improvement of symptoms, brain imaging, the rate of shunt failure, complications, together along with the adverse events throughout the study would be investigated. The study could provide evidence for the selection of treatments for patients with INPH and may generate discussion about the optimal treatment. Despite of the strengths, there are still some questions that need to be discussed.

The diagnosis of INPH remains controversial since the lack of widely accepted and standardized criteria. Marmarou et al first proposed the evidence-based guidelines for clinical diagnosis of INPH in 2005 (Western guideline).^[18]^ Japanese Society of Normal Pressure Hydrocephalus published the English edition of the Guidelines for Management of Idiopathic Normal Pressure Hydrocephalus in 2008 (Japanese guideline), which was then updated in 2012.^[19]^ Despite of the fact that there are some differences between Western guideline and Japanese guideline, it is rather widely accepted by many clinicians that the diagnosis of INPH should be classified into probable, possible, and unlikely categories based on clinical history, symptoms, and brain imaging, and an accurate diagnosis of INPH depends upon the response to shunting.^[18]^

After the description of the triad of syndrome by Hakim and Adams, the clinical symptoms of INPH are essential regarding its diagnosis, among which gait/balance disturbance tends to be the most readily recognized and common while cognition defects and urinary symptoms do not occur in all patients. As a consequence, either Western guideline or Japanese guideline suggested the probable INPH patients should present at least 2 symptoms of Hakim-Adams syndrome and gait/balance disturbance must be present.

Ventriculomegaly (Evans index >0.3) is another common and obligate feature of INPH. Recently, a great deal of attention is given to the radiological sign of Disproportionately Enlarged Subarachnoid Space Hydrocephalus (DESH sign, high convexity tightness and dilated sylvian fissure with ventriculomegaly) on coronal magnetic resonance imaging, which could be used to distinguish INPH from other neurological disorders, such as Parkinson's disease and Alzheimer's disease.^[19]^

In terms of the definition of “normal pressure,” it is different between Western guideline and Japanese guideline. The CSF opening pressure measured by lumbar puncture in the lateral recumbent position is in the range of 70 to 245 mm H_2_O according to the Western guideline, comparing to a CSF opening pressure under 200 mm H_2_O based on Japanese guideline. Taken together, a range of 70 to 200 mm H_2_O is considered in this study since pressures that are dramatically higher or lower than this range are not accordant with a probable NPH diagnosis, as well as not suitable for the upcoming LPS surgery.

This trial will the first randomized controlled trial that compares the long-term outcomes of VPS with that of LPS in the treatment of INPH. The results of this trial will provide certain evidence for the treatment option for patients with INPH. This trial will also generate the discussion regarding this subject. In addition, based on this trial, we could analyze the related factors of shunt failure in patients with INPH to exclude the patients with high risk of shunt failure.

This trial has some limitations. First, it is single-center study. Second, the shunting outcomes are possibly associated with personal experiences and qualifications. In this regard, we will propose a uniform standard and surgeons will be trained before recruitment.
